### Randomization, allocation concealment, and blinding

All participants will be randomly allocated into the intervention or control group in a ratio of 1:1. The randomization list of each ED patient will be generated by a computer, which is calculated by a statistical expert from the Faculty of Medical Statistics and Epidemiology, Ningxia Medical University. A sealed envelope will be used to store the randomization schedule which will be restricted in a dedicated research office to maintain confidentiality. In order to make sure of “double-blind” conditions, no data collectors or investigators have access to the data distribution. Only the project manager who will be responsible for gas distribution can consult this information. Ningfeng Oxygen Company packages the two gas mixtures in strictly identical-looking gas cylinders, one containing nitrous oxide/oxygen and the other oxygen. Therefor, all the gas cylinders will be identified only with a label (A or B). Patients given the letter A will be treated using a canister with the appropriate letter containing premixed nitrous oxide/oxygen. Those with the letter B will be given oxygen. Before and during the treatment period, the patient, the investigator, and the data collector are also blind to what is in each canister and what the letters A and B stand for. The rules were that the cessation of blinding would take place by the project manager only, after the completion of all the trials.

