### Study participants

All trauma patients who present to the ED will be invited to participate. The specific inclusion criteria are: patients who speak Chinese; aged ≥ 18 years; report moderate to severe intensity of acute pain upon admission (defined as a pain score ≥ 4 according to the Numerical Rating Scale [NRS]); are able to take deep breaths to use the self-managed device; are willing to participate in the study and sign informed consent. Patients are ineligible if they have considered contraindications to using the premixed gas (intracranial hypertension, recent ophthalmic surgery, epilepsy, unconsciousness, pneumothorax / hemothorax, facial traumas, intestinal obstruction, pulmonary embolism, emphysema, sinusitis, and retinal detachment [17]). Other exclusion criteria are: recent receipt of analgesics within 6 h; life-threatening situations or instability of clinical vital signs; pregnancy; individuals in police custody; or individuals included in another study.

All participating clinicians will be associate chief physicians, will have worked in the ED for > 5 years, and will be willing to participate in and receive training from the originator who conceived and designed the protocol. In this trial, two fixed clinicians who meet all the above criteria will be included.

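### With one fixed letter per arm, the same staff can work out the A/B code from pain relief and carry it over to later patients

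*Protocol article*

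**What the plan says.** All the coding statements are in the Protocol article under *Randomization, allocation concealment, and blinding*.

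- **Label:** "all the gas cylinders will be identified only with a label (A or B". No second identifier is described.
- **Meaning of the letters:** "Patients given the letter A will be treated using a canister with the appropriate letter containing premixed nitrous oxide/oxygen", and "Those with the letter B will be given oxygen".
- **Who is said not to know it:** patients, investigators and data collection staff alike. For the last of these it says: "the data collector are also blind to what is in each canister and what the letters A and B stand for".
- **Who holds the list and breaks the blind:** "Only the project manager who will be responsible for gas distribution can consult this information", and "the cessation of blinding would take place by the project manager only, after the completion of all the trials".

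Other sections bear on who could learn the code. *Study participants* provides for two fixed clinicians, who are to "receive training from the originator who conceived and designed the protocol". *Data collection, management, and confidentiality* says the data collectors and investigators also stay the same throughout. *Primary outcome measure* has the data collector record a pain score that the patient gives on the NRS.

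**The concern.** A code with one letter per arm never changes, so whatever staff learn about a letter from one patient also applies to the next patient with that letter. Because the same few people see all patients, this evidence accumulates. The article also prints the key beside the statement that staff do not know it, so any staff-facing text that repeats the passage would give the code away directly.

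The primary outcome is subjective. Staff prepare and support the patient before inhalation, ask about discomfort during it, record the score, evaluate adverse effects and may decide whether to continue after an undesirable event. Healthcare providers also rate their own satisfaction. Knowing the arm can influence each of these. Bias that enters while a self-reported score is collected cannot be removed at analysis.

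**Working it through.** The plan gives no figure for the strength of the blind, so there is none to reproduce. The check asks how quickly the letters can be decoded if the protocol's own expectations are true.

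**Inputs** (*Sample size determination*; *Randomization, allocation concealment, and blinding*)
- Pain relief at T1: 65% with nitrous oxide/oxygen, 8% with oxygen.
- Pain relief at T2: 70% and 10%.
- 90 patients, 45 per arm, allocated 1:1, one letter per arm.

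**Step 1: a single responder.** Before any data, either letter is equally likely to be the active gas. After one patient with relief, the probability that this patient's letter is the active gas is p1/(p1 + p2):
- T1: 0.65/(0.65 + 0.08) = 0.890
- T2: 0.70/(0.70 + 0.10) = 0.875

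This is suggestive but not decisive.

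**Step 2: a tally by letter.** Suppose staff have seen k patients on each letter and guess that the letter with more responders is the active gas, tossing a coin on ties. With X ~ Bin(k, p1) and Y ~ Bin(k, p2), the probability of a correct guess is P(X > Y) + ½·P(X = Y).

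For k = 1 at T1:
- P(X > Y) = 0.65 × 0.92 = 0.598
- P(X = Y) = 0.65 × 0.08 + 0.35 × 0.92 = 0.374
- Correct guess = 0.598 + 0.374/2 = 0.785

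The same formula for larger k gives:

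| Patients per letter | Patients seen | T1 rates | T2 rates |
|---|---|---|---|
| 1 | 2 | 0.785 | 0.800 |
| 2 | 4 | 0.892 | 0.902 |
| 3 | 6 | 0.941 | 0.948 |
| 5 | 10 | 0.981 | 0.984 |
| 10 | 20 | 0.9985 | 0.9989 |

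**Step 3: who is then exposed.** After five patients per letter, 10 of 90 have been treated and 90 − 10 = 80 are still to come. After ten per letter, 90 − 20 = 70 are still to come. Scores already recorded are not affected.

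**Step 4: the same event under unique codes.** If each patient has a separately coded cylinder, learning one patient's gas directly reveals 1 of 90 (1.1%). If a cylinder serves several patients, it reveals only those. Nothing can be tallied by letter.

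**The case against.** The strongest reply is that the article is written for readers, and can explain a code that staff are never given. This stands. The sentence on clinicians' training names the trainer, not the content. The training topics listed under *Data collection, management, and confidentiality* do not include the letter key. A reader might infer that staff are taught what A and B mean, but the document does not show it.

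A reader might also infer that one unmasked patient unmasks all 90. That goes too far for three reasons:
- A patient who guesses learns only their own gas.
- Among staff, only those who see letters across patients can carry the knowledge over, and only to patients treated later.
- One responder gives a probability of about 0.89, not certainty. Both arms also receive conventional pain treatment, so relief or drowsiness need not come from the gas.

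The protocol does have real protections: identical-looking cylinders, a sealed and restricted schedule, and unblinding by the project manager only. Additional pain management is allowed only after the intervention, so for a full 15-minute course it cannot affect the T1 or T2 scores. It would therefore be wrong to say that blinding is absent or that the trial cannot be called double-blind.

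Finally, unique codes do not stop staff from guessing an individual patient's gas from its effects. That is correct and limits what the fix can achieve. None of these replies removes the carry-over that a fixed two-letter code permits.

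**Conclusion.** The point holds as a weakness in the coding scheme that is cheap to repair. If the planning rates are right, fixed staff who tally relief by letter would have the code with probability about 0.79 after one patient per letter, 0.98 after five and over 0.99 after ten. Most of the trial could then be run by people who effectively know the arm of each patient whose letter they see.

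This rests on four assumptions:
- Staff see both the letter and the response.
- They compare responses across patients.
- Patients respond independently.
- The planning rates, which come from 20 preliminary patients, are about right. A smaller true difference would slow the decoding.

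The calculation uses pain relief alone. Recognisable gas effects could add to it but are not quantified. The document shows neither that staff have the printed key nor that decoding has occurred, and the resulting bias in NRS scores cannot be sized from it.

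**What to change.** 1. Replace the letters on all remaining cylinders with a unique, non-sequential code for each cylinder.
2. Have the statistician and the gas supplier hold the code-to-content list, outside recruitment and assessment. Give the project manager only the cylinder code for each randomised patient. Revise the sentences on access and unblinding to match, because the project manager would no longer hold the key.
3. Keep the letter-to-gas key out of any text that staff or patients can see.
4. Recruitment began in November 2017, so report the date of the change and who knew the key before it. Any comparison of the primary result before and after the change is descriptive only, because the groups would be small and the change is confounded with calendar time.
5. Word the double-blind claim to say that the coding prevents carry-over between patients but cannot exclude guesses from gas effects. Recording treatment guesses from patients and data collectors would show how far such guessing goes.

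The cost is relabelling, one lookup list, a short amendment and slightly more stock handling for the supplier and project manager. The sample size does not change.

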### Measurement

The investigator will record participants’ characteristics, demographic data (age, sex, nationality, weight, and height), and physiological parameters (pulse rate, blood pressure, and oxygen saturation). Other information regarding pain score, diagnosis of traumatic injury, total length of gas inhalation, analgesic prescription, adverse effects, satisfaction of patients and healthcare professionals, as well as the acceptance from patients will be recorded by the researcher.

Self-assessment of pain severity will be measured with the NRS. The NRS is a tool with great reliability and validity that is frequently used for assessing pain level from zero (painfree) to ten (worst pain intolerable) [31]. The physical parameters will be monitored via an electronic manometer (OMRON, HEM-7120) and OXIMETER (PC-60B). The evaluated pain score along with non-invasive monitoring of blood pressure, heart rate, and digital monitoring of oxygen saturation at baseline (T0) before the intervention, 5 min (T1), and 15 min (T2) after the beginning of the intervention, and at 5 min (T3) after the intervention.

Any observed adverse effects of the fixed nitrous oxide/oxygen mixture and oxygen will be carefully evaluated and recorded by the investigator after the beginning of the gas administration. The prospectively occurred adverse effects include gastrointestinal adverse effects (vomiting, nausea), respiratory adverse effects (oxygen desaturation which defined as pulse oximetric saturation ≦ 94%, arterial hypotension, and bradycardia), and any other discomfort (numbness, dizziness, drowsiness, oversedation, and headache) [32]. If any adverse effects take place, patients will be given inhaled oxygen and in < 5 min the adverse effects will vanish. All severe adverse effects and management of them during the gas inhalation will also be noted.

Both patients’ and healthcare providers’ satisfaction with pain administration under the new analgesia will be investigated by a five-point satisfaction scale (5, very satisfied; 4, satisfied; 3, uncertain; 2, dissatisfied; 1, very dissatisfied) [33]. Moreover, the acceptance will be obtained by asking patients whether they would accept the same gas inhalation in case of another trauma with moderate to severe pain (yes / no). The satisfaction and the acceptance are recorded at T3.

The clinical demographic data, details of trauma type, and analgesic prescription will be obtained from medical records using a standardized case report form.

### Outcome measures

#### Primary outcome measure

The primary outcome measure will be the level of pain relief after the initiation of the intervention, which is assessed and recorded by the data collector according to the pain level provided by patients using a self-assessment scale (NRS).

#### Secondary outcome measures

Secondary outcome measures include physiological parameters, adverse events, overall satisfaction from both patients and healthcare professionals, acceptance from patients, and total time of the gas administration.

### Sample size determination

Based on our previous studies on cancer breakthrough pain and burn-dressing pain [32, 34], this study uses pain severity as the primary endpoint measure for sample size calculation. We used preliminary visits obtained in our ED for 20 patients and calculated the sample size at 5 min (T1) and 15 min (T2) after the beginning of intervention. It is observed that 65% of patients receiving premixed nitrous oxide/oxygen had pain relief at T1 compared with 8% of patients receiving oxygen (a decrease in pain intensity of at least 30% was recommended as the pain relief [35]). We found that 70% of patients in the experimental group experienced pain relief at T2 versus 10% in the control group. It aimed to determine a appropriate target sample size that would provide a 90% power (*β* = 0.10) for two-tailed testing with 5% type-1 error rate of the measure. We separately calculated a minimum requirement of 30 patients or 24 patients for total with the formula [36, 37]. In practice, we finally decided on 90 samples (45 per group) to improve the power of this study.

### Recruitment

In this trial, participants will be recruited at the ED of General Hospital of Ningxia Medical University. This medical center is the largest hospital in Ningxia Hui Autonomous Region. It is well-known in the northwestern region of China for its comprehensive disciplines, powerful technology, advanced medical equipment, outstanding specialties, and strong multidisciplinary advantages. Furthermoremore, according to the ED census data of 2016, there is a sufficient patient source in this hospital. Thus, in this selected clinical center, it is feasible to reach the target sample size.

### Participant retention and withdrawal

As soon as a participant is enrolled, the research team are responsible for achieving a low rate of loss to intervention. Patients have the right to withdraw from the study at any time and this will not affect their subsequent treatment. The Data Monitoring Committee (DMC) will discuss and analyze the reason of dropout with the data collectors, which will be documented on a standardized pro forma.

### Data collection, management, and confidentiality

All members involved in the research team will receive group training sessions before the study. Training will include study design (e.g. require double-blind), intervention process (e.g. inhaling gases via facemask), assessment of the outcome measures (e.g. standardized procedures to assess), and recorded data (e.g. training for the use of a unified data collection form in detail). Furthermore, the trained data collectors and investigators are fixed during the implementation of interventions and through the double-entry method for data quality control. The members of the DMC and the auditor will inspect this database regularly to promote data quality (see “Data monitoring” and “Auditing”). Using a Microsoft Access database (Microsoft Office 2010, Redmond, WA, USA) to accomplish all study data input.

Throughout the trial, participants are anonymized. All participants’ personal information (e.g. name and patient identification number) will be kept in a separate locked cabinet and will be entered into the password-protected Microsoft Access database. Only research team members can access this personal data with reasonable request and consent of the project manager. A separate code, generated by pre-randomization, will enable anonymized data to be identified and this unique identifier will be maintained by the project manager. Anonymized trial data will be stored securely in another Microsoft Access database. The trial data collectors, the investigator, and the members of the DMC can access the trial data for the final statistical analysis.

### Data monitoring

This trial will be overseen by a DMC, which is independent from the sponsor and competing interests. Members consisted of one clinician, two nurses working in the ED, one pain management specialist, and a senior academic statistician who acts as the committee’s chair. The DMC will meet regularly to monitor the trial progress and guarantee protocol adherence. They are also responsible for checking for the reason of the participant withdrawal from this trial, assessing safety issues, and if there are any reasons that the trial should discontinue or make amendments.

### Auditing

The trial funder will apply audits annually and inspect the source data to verify the accuracy, completion, validity, and safety of the data. The auditing will potentially include the utilization of funds, the essential documents, the trial progress, and the participants’ medical records.

### Data analysis

SPSS version 22.0 (Chicago, IL, USA) will be used to conduct the statistic analysis, initially according to the intention-to-treat principle. All patients randomized should be included in the analysis and missing data will be handled using multiple imputation. Descriptive statistics will be adopted to describe the population demographic data by medians (interquartile ranges [IQR]; min–max), means (standard deviations), and proportions (exact binomial 95% confidence intervals [CIs]), as appropriate. The comparison of means will be assessed by Student’s *t* test or non-parametric test and using the Mann–Whitney test to compare means of continuous variables if applicable. Chi-squared tests or Fisher’s exact test will be performed to compare the proportions of categorical variables. The analysis of physiological parameters and scores at baseline, T2, and T3 were performed by analysis of covariant (ANCOVA) adjusting for the respective baseline value on the two groups (“experimental” and “control”). We considered all *P* values < 0.05 to be statistically significant.

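### Multiple imputation is paired with tests of proportions (chi-squared or Fisher) that, as named, give nothing to pool by Rubin's rules; a poolable effect measure should be stated

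*Protocol article*

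**What the plan says.** All of the analysis wording stands in the Data analysis section of the protocol article.

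- Missing data: "All patients randomized should be included in the analysis and missing data will be handled using multiple imputation".
- Proportions: "Chi-squared tests or Fisher’s exact test will be performed to compare the proportions of categorical variables". No risk difference, odds ratio or model is named for a binary outcome.
- Continuous variables: Student's t test or a non-parametric test, "using the Mann–Whitney test to compare means of continuous variables if applicable".
- Repeated measures: "The analysis of physiological parameters and scores at baseline, T2, and T3 were performed by analysis of covariant (ANCOVA"), adjusted for the respective baseline value. T1 is not in this list, although the Abstract makes T1, T2 and T3 all time points of the primary outcome.

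The Primary outcome measure section says: "The primary outcome measure will be the level of pain relief after the initiation of the intervention", taken from the NRS. The Sample size determination section turns this into a proportion: "a decrease in pain intensity of at least 30% was recommended as the pain relief", with 65% v 8% expected at T1 and 70% v 10% at T2.

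**The concern.** Multiple imputation produces several completed data sets. The usual inference takes an estimate and its standard error from each and combines them by Rubin's rules, so that the variance between imputations enters the test. A t test and an ANCOVA supply both quantities. Chi-squared supplies a statistic, and Fisher's exact test supplies a P value.

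The comparison affected is a central one. By elimination, the relief proportion goes to chi-squared or Fisher, as do acceptance (yes/no) and adverse events. T1 scores, absent from the ANCOVA list, could go to Mann–Whitney.

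The article fixes both the missing-data method and the tests, and the two do not fit together as written. Anyone who followed the wording would have to add a combination rule or change the test. The risk is that an analyst holding several P values takes a shortcut that ignores the imputation variance, so that the error rate is no longer the stated 5%.

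**Working it through.** The plan gives no figure on this point to reproduce. The inputs are 45 per arm, 1:1 allocation and a two-sided 5% level, all from the article. The documents give no missing rate, so 5%, 10% and 20% are assumed, missing completely at random and equally in both arms, with imputation within arm.

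**What each named test yields**

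| Test | Output per imputed set | Combination |
|---|---|---|
| t test, ANCOVA | estimate and SE | Rubin's rules directly |
| Chi-squared | statistic | D2 rule, not Rubin's rules directly |
| Mann–Whitney | statistic | through its z, or the probability index with its SE |
| Fisher's exact | P value | no standard rule |

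**Why a single imputed set misleads.** Let V be the variance of the risk difference with complete data and f the fraction missing.

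- Variance of the difference from observed data: V/(1 − f).
- Variance added by one proper imputation: B = V·f/(1 − f).
- True variance of the difference in one completed set: V(1 + f)/(1 − f).
- Variance that the ordinary test assumes: V.

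The test statistic therefore has standard deviation √[(1 + f)/(1 − f)] under the null, and the false-positive rate is P(|Z| > 1.96/√[(1 + f)/(1 − f)]):

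- f = 5%: 1.05/0.95 = 1.105, root 1.051, cut-off 1.864, rate 6.2%.
- f = 10%: 1.10/0.90 = 1.222, root 1.106, cut-off 1.773, rate 7.6%.
- f = 20%: 1.20/0.80 = 1.500, root 1.225, cut-off 1.600, rate 11.0%.

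Simulation of an uncorrected chi-squared test on one imputed set, with true relief of 10–50% in both arms, gives about 6–7%, 7–9% and 10–12% at the three rates. At 2% missing it gives about 5–6%.

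**Why pooling works.** Rubin's total variance with m imputations is V + (1 + 1/m)B. The true variance of the pooled difference is V/(1 − f) + B/m. Since V/(1 − f) = V + B, the two are equal. With m = 5 and f = 20%, B = 0.25V, and both are 1.30V.

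**Simulated size of the pooled tests under no effect**

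- Risk difference by Rubin's rules: 4.7–6.0% (20 imputations, 2–20% missing); 4.5–6.3% with 5 imputations.
- Chi-squared by D2: 4.5–5.8% (20 imputations, 2–20% missing).
- Mann–Whitney pooled z: 4.6–4.8%; probability index: 4.9–5.4% (20 imputations, 5–20% missing).

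At the planned 65% v 8%, the pooled risk difference and the D2 test each rejected in all 500 simulated trials at every missing rate tried.

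**The case against.** The strongest case on the other side has four parts.

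1. A reader might infer that no valid combined P value exists. That is not so. D2 combines chi-squared statistics, a risk difference or log odds ratio answers the same two-by-two question, and a Mann–Whitney z can be pooled. All that were simulated hold about 5%. This stands.
2. A reader might infer that pain scores are tested by Mann–Whitney. The Data analysis section sends scores at T2 and T3 to baseline-adjusted ANCOVA, which pools directly. Mann–Whitney is only a fallback, and at most T1 could fall to it. This stands.
3. The number of imputations, the imputation model and the pooling rule are commonly left to a full protocol or SAP, which is not shown. Their absence is indeed no finding. What remains is that the article itself names chi-squared or Fisher as the tests for proportions, beside multiple imputation, with no effect estimate to pool.
4. Nothing in the article proposes a shortcut. Testing one set, counting any of five as significant (about 9–24% false positives) or stacking the sets (about 40–45%) would be analyst errors. Averaging P values, another shortcut, inflates little (5–7%). This stands too: the figures show what is at risk and do not describe the plan.

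The article gives some reason to expect missing values, since patients may ask to stop the gas or withdraw at any time. But inhalation lasts at most 15 minutes and the last reading is 5 minutes later, so heavy loss is not shown to be likely.

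**Conclusion.** The point holds in a limited form. The stated missing-data method and the stated tests for proportions do not fit together, and this touches the relief comparison on which the trial is sized. A valid combined test is available but is not the one named, and Fisher's test in particular has no standard route.

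The documents do not support saying that the planned type 1 error is inflated. Inflation arises only if a shortcut is taken. For a single imputed set it is about 6–12% at 5–20% missing, an assumed range, for chi-squared with data missing completely at random. Fisher's test is conservative, so it would show less. With little missing over about 20 minutes the effect is small, and with nothing missing it vanishes. At the effect assumed in the sample size section the conclusion would not change. The wording is worth correcting, but the practical impact is probably small.

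**What to change.** For the imputed analysis:

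- Compare 30% relief by a risk difference with its standard error in each imputed data set, pooled by Rubin's rules. Preferably obtain it by standardisation from a logistic model with arm and T0 NRS. An unadjusted pooled risk difference, or D2 on the planned chi-squared, would also give a valid test.
- Extend the planned baseline-adjusted ANCOVA of NRS to T1, and pool it the same way at T1, T2 and T3.
- Keep chi-squared, Fisher and Mann–Whitney for observed data only, labelled as sensitivity analyses.

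The cost is a few sentences in the analysis section and a little more analysis work. All the data needed, including T0 NRS, are already to be collected.

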## Methods/design

### Aim

The primary aim of the current study is to determine the clinical analgesic effect of the fixed nitrous oxide/oxygen mixture on trauma patients with acute pain when compared with the control group. It is measured by pain relief level. Secondary objectives of this trial include:Evaluating the clinical use safety of the fixed gas by physiological parameters and adverse effects.Assessing the satisfaction of both patients and healthcare workers with pain treatment.Investigating patients’ acceptance for the new analgesia method.

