### Study design

This is a single-center, prospective, randomized, double-blind, placebo-controlled, two-arm, superiority study. It was designed to test the analgesic effect and safety of inhaling premixed nitrous oxide/oxygen use in adult trauma patients with moderate to severe acute pain. This protocol was drafted using the SPIRIT guidelines [30] (see Additional file 1) and following the checklist of the Consolidated Standards of Reporting Trials (CONSORT) statement (see Additional file 2). The clinical trial was reviewed and approved by the Ningxia Medical University Ethics Committee. This study has been registered at Chinese Clinical Trial Registry (registration no. ChiCTR-INR-16007807). The whole study design is provided in Fig. 1. Additionally, a SPIRIT figure for the schedule of enrolment, interventions, and assessments is presented in Fig. 2.

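### The trial says it tests safety, but a chi-squared or Fisher P value with 45 per arm cannot support a favourable statement on uncommon adverse effects; risk differences with 95% CIs should carry it

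*Protocol article*

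**What the plan says.** Under Study design, the protocol article calls the trial a superiority study and states: "It was designed to test the analgesic effect and safety of inhaling premixed nitrous oxide/oxygen use in adult trauma patients". Under Aim, safety is a secondary objective: "Evaluating the clinical use safety of the fixed gas by physiological parameters and adverse effects". Adverse events are accordingly a secondary outcome: "Secondary outcome measures include physiological parameters, adverse events, overall satisfaction from both patients and healthcare professionals". The Measurement section lists the adverse effects by type, among them vomiting, nausea, desaturation, hypotension, bradycardia, dizziness, drowsiness and oversedation.

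The size of the trial comes from efficacy only. Sample size determination says "this study uses pain severity as the primary endpoint measure for sample size calculation", with "two-tailed testing with 5% type-1 error rate of the measure" and 90% power. It arrives at 30 or 24 patients in total and then adopts 90 (45 per group).

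Data analysis does not mention adverse effects by name. The rule that covers yes/no outcomes is "Chi-squared tests or Fisher’s exact test will be performed to compare the proportions of categorical variables", with P "values < 0.05 to be statistically significant". Exact binomial 95% confidence intervals appear there only in the sentence on describing demographic data. Physiological parameters have their own baseline-adjusted ANCOVA. Under Data monitoring, a Data Monitoring Committee (DMC) assesses safety issues.

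**The concern.** A superiority test asks whether the arms differ detectably. A favourable safety statement needs something else: evidence that any excess harm is no larger than some amount. The stated rule for proportions yields a P value and no bound on the excess, and the sample size was not chosen with adverse effects in mind. For any uncommon effect a non-significant result is then close to the default, whatever the gas does.

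What is at stake is how the safety aim is reported. The Discussion foresees preliminary guidelines and, in the abstract, wide use if the treatment succeeds. A safety statement resting on a non-significant test in 45 per arm would add little evidence to that case while appearing to add a good deal.

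**Working it through.** **Inputs from the protocol article.** 45 per arm, 1:1 allocation, two-sided 5%, chi-squared or Fisher's exact test. Pain-relief rates for sizing: 65% vs 8% at T1 and 70% vs 10% at T2, 90% power. No adverse-effect rate is given, so the oxygen-arm rate is an assumption, varied below.

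**The plan's own figures.**
- T1, simple pooled formula: n = (1.960 + 1.282)² × 2p̄(1 − p̄) / (p₁ − p₂)², with p̄ = 0.365. This is 10.507 × 0.46355 / 0.3249 = 14.99, so 15 per arm and 30 in total, as stated.
- T2, formula with separate null and alternative variances, p̄ = 0.40: [1.960 × √0.48 + 1.282 × √0.30]² / 0.36 = 11.8, so 12 per arm and 24 in total, as stated.

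No single formula tried gives both figures. That is immaterial here, because 45 per arm gives over 99.9% power for those pain-relief rates. Neither figure concerns adverse effects.

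**Chance of missing a harm with 45 per arm.** All 46 × 46 possible outcomes were enumerated:

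miss rate = 1 − Σₐ Σ_b Bin(a; 45, p_gas) × Bin(b; 45, p_oxygen) × 1[P(a, b) < 0.05]

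| Assumed rates, oxygen → gas | Missed, Fisher | Missed, uncorrected chi-squared |
|---|---|---|
| Doubling 2% → 4% | over 99% | 95% |
| Doubling 5% → 10% | 94% | 84% |
| Doubling 10% → 20% | 82% | 72% |
| Doubling 20% → 40% | 54% | 44% |
| Doubling 30% → 60% | 24% | 18% |
| Tripling 2% → 6% | 98% | 87% |
| Tripling 5% → 15% | 77% | 61% |
| Tripling 10% → 30% | 43% | 31% |
| Tripling 20% → 60% | 3% | 2% |

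Power passes 50% for a doubling at an oxygen-arm rate of about 21% (Fisher) or 18% (chi-squared). For a tripling it does so at about 9% or 7%. For scale, 80% power would need about 435 per arm for 5% vs 10% and 141 per arm for 5% vs 15%.

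**What an interval shows that the P value does not.**
- 2/45 in each arm: P = 1.0, but the Newcombe 95% CI for the risk difference runs from −11 to +11 percentage points.
- 5/45 on the gas vs 0/45 on oxygen: Fisher P = 0.056, Newcombe 95% CI +1 to +23 points. Uncorrected chi-squared gives P = 0.021. The expected count per arm is 5 × 45/90 = 2.5, below 5, where Fisher is the usual choice. The verdict here turns on which of the two named tests is used; the interval does not.
- 0/45: the exact two-sided 95% upper limit is 1 − 0.025^(1/45) = 7.9%.

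**The case against.** The strongest reply has four parts.

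1. **The stronger reading is not in the text.** A reader might infer that the protocol treats a non-significant adverse-effect comparison as proof of safety. It nowhere says so, and its statements about guidelines are conditional on the treatment succeeding. This stands: the point is only that such a result could be read that way and that the plan does not guard against it.

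2. **Safety is assessed by more than one test.** Physiological parameters, including saturation, blood pressure and heart rate, are analysed by ANCOVA, and the DMC reviews safety. This also stands. The point is confined to adverse-effect proportions, and neither element gives an interval for a difference in those.

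3. **The power loss is not universal.** A reader might infer that any doubling or tripling of harm is usually missed. The table does not support that: a tripling is usually detected from an oxygen-arm rate of about 9% upward, and a doubling from about 18–21%. The protocol gives no basis for assuming that effects such as dizziness or drowsiness are rare.

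4. **Adverse-effect reporting is commonly left to the analysis plan, and most trials of this size have low power for harms.** The absence of a margin or interval from a condensed article is indeed no error in itself, and low power for a secondary outcome is ordinary. What remains is that the article does fix a between-arm method for proportions, and that method does not suit a design said to test safety. If the full protocol or analysis plan already specifies risk differences with intervals, only the Study design wording needs attention.

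**Conclusion.** The point holds for adverse-effect proportions. A chi-squared or Fisher test at P < 0.05 with 45 per arm cannot support a favourable safety statement about uncommon harms: at an assumed oxygen-arm rate of 5%, a doubling is missed in 94% (Fisher) or 84% (chi-squared) of trials and a tripling in 77% or 61%. The size depends on rates that the protocol does not give, and it falls quickly as the oxygen-arm rate rises. The conclusion about method does not depend on those rates, since a non-significant P value never bounds the excess harm. The primary pain-relief comparison, the ANCOVA of physiological parameters and the DMC review are unaffected.

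**What to change.** In Data analysis, add that each listed adverse effect, any adverse effect and severe adverse effects will be reported as counts by arm, with the risk difference and its 95% CI (for example Newcombe). Where no event is seen in an arm, report the exact upper bound (7.9% for 0/45). State that safety statements will rest on these intervals and that P > 0.05 will not be taken as evidence of safety.

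In Study design, say that the trial tests the analgesic effect and describes safety.

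This takes a few sentences and needs no further patients or data. The downside is a more guarded safety claim.
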